**Dissemination and explanation of blood results**

All non-immunology blood results will be given and explained to all parents after screening and at follow-up visits. Immunology results will be explained in general terms, for the group and not for individuals, at the end of the study. Those with abnormal blood results at screening will be offered appropriate investigations and treatment or referral as necessary. Parents will receive an explanation of all screening results before proceeding with MVA.HIVA immunization.

**6.2 Study Visits**

## **CONFIDENTIAL**

**Sensitisation and Informed Consent:** The majority of children will be sensitised at birth or in the 1st few weeks of life. If sensitised at birth the study will be explained after the mother has had sufficient time to recover from the labour, and parents will be invited to ask questions. If the parents express an interest in taking part in the study their child will be assigned a 3-digit sensitisation number and told that they will be invited to return to the clinic when their child has reached 16 weeks of age to discuss their interest and potential eligibility for participation in the study. If they are found to be willing and eligible at this visit, parents will be asked to sign/thumbprint the informed consent form. The research physician must be available to answer any questions during the informed consent process, and is the person designated to sign the informed consent form. The consent form must also be signed by an independent witness who will be present during the consent process. The mother will undergo voluntary counselling and testing (VCT) for HIV by the trained study physician at Sukuta Health Centre. A VCT trained field worker will be available to translate during this process in a language that the mother understands.

**HIV Positive Women:** Any women who tests positive for HIV will be followed up and managed for their HIV at Sukuta Health Centre where practicable for 3 years. Her child will be offered an HIV PCR test and treatment and follow up as appropriate. Sukuta Health Centre will act as the first point of clinical contact for those women found to be HIV infected during this study, however they will also need to enrol into a government accredited HIV clinic as part of the National HIV Programme. The choice of clinic will be decided on a case-by-case basis in consultation with the mother according to their situation and preference.

### **Visit 1 – SCREENING VISIT (Infant aged 16 weeks $\pm$ 10 days)**

- Subjects will be brought to the vaccine trial clinic.
- Consent to participate in the study will be obtained.
- An interim medical history will be taken.
- Physical examination including vital signs (temperature, respiratory rate, pulse rate), and anthropometry (weight, mid left upper arm circumference (MUAC), length) will be performed by the research field worker / research nurse.
- EPI vaccines appropriate for age will be given (Pentavalent, PCV-7 and OPV).
- Appointment given for 3 weeks time.

### **Visit 2 – BASELINE VISIT (Infant aged 19 weeks $\pm$ 10 days)**

- Subjects will be brought to the vaccine trial clinic.
- Continued consent to participate in the study will be confirmed.
- Inclusion and exclusion criteria will be checked.
- An interim medical history will be taken.
- Physical examination including vital signs (temperature, respiratory rate, pulse rate), and anthropometry (weight, mid left upper arm circumference (MUAC), length) will be performed by the research field worker / research nurse.
- 5 mL of venous blood will be collected for baseline FBC, biochemistry, pre-MVA.HIVA immunogenicity and EPI vaccine antibody assays.
- Appointment given for 1 week time.

### **Visit 3 – VACCINATION VISIT, MVA.HIVA vaccination day (Infant aged 20 weeks $\pm$ 10 days)**

## CONFIDENTIAL

- Subjects will be brought to the vaccine trial clinic.
- Continued consent to participate in the study will be confirmed.
- Inclusion and exclusion criteria will be checked.
- Results of FBC and biochemistry from previous week will be reviewed by the research physician to ensure the child is eligible for randomisation.
- An interim medical history will be taken.
- Physical examination including vital signs (temperature, respiratory rate, pulse rate), and anthropometry (weight, mid left upper arm circumference (MUAC), length) will be performed by the research field worker / research nurse.
- The screening safety profile will be reviewed by the research physician and those children that fulfill all inclusion criteria and no exclusion criteria will be randomised to one of the two study groups by selecting an envelope containing the block randomized treatment group that they are in:
  - **Group 1** infants will receive MVA.HIVA ( $5 \times 10^7$  pfu in no more than 100 µl) intramuscularly into the deltoid muscle of the left arm with a BCG scar. The injection site will be covered after 10 minutes with a sterile dressing that will be removed at the one-hour observation.
  - **Group 2** (control) will not receive any vaccines.
- The infant and parent will remain at the clinical area for one hour following vaccination and will then be allowed to return home.
- The injection site will be inspected at 10 minutes when a dressing will be applied.
- Vital signs will be checked at 30 minutes (+/- 5 min) and 1 hour (+/-10 min) post injection.
- At 1 hour (+/-10 min) the dressing will be removed and discarded. The largest diameter of any induration or redness and any other local reaction at 1 hour will be documented into the CRF. An assessment for possible systemic adverse events (AE's) will be carried out and documented on the CRF, and any concomitant medication documented.
- A nurse / field worker will visit subjects at home daily for the first two days after MVA.HIVA vaccination to record safety and reactogenicity data on a standard CRF form.

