### **4 STUDY DESIGN**

This is an open randomized phase I study evaluating the safety and immunogenicity of a single dose of MVA.HIVA vaccine administered at 20 weeks of age to infants born to HIV-1/2-uninfected mothers, and its gross impact on the immunogenicity of EPI vaccines administered not less than 4 weeks before. The immunology laboratory staff will be blinded for the study product / control group allocation.

**Study site:** Sukuta Health Centre, The Gambia

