**CONFIDENTIAL****4.2 Randomisation**

Infants who have been sensitised into the study will be invited to attend Sukuta Health Centre at 19 weeks of age. Those with a documented BCG vaccination within the first two weeks of life who have received all their EPI vaccines on schedule at the Sukuta Health Centre will be eligible for recruitment. Parents of those infants who meet all inclusion and none of the exclusion criteria will be asked to sign the informed consent form. A baseline blood sample will be taken and they will be asked to return to the Health Centre at 20 weeks of age. When they return for their 20 week visit the blood results will be checked and providing they still meet the inclusion and exclusion criteria they will be randomised to one of the two study groups of 24 (Table 4) by picking the next envelope (block randomised). The sensitisation number and allocation to vaccine group will be entered into the enrolment log. This will assign them to one of the two treatment groups: Group 1 will receive MVA.HIVA and Group 2 will not receive any vaccines. Infants recruited into this study will receive their routine EPI and study vaccines from the study team in order to reduce confounding variables that might result from variations in age at vaccination, and batch of vaccines administered.

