**5.2 Exclusion Criteria**

- a. Acute disease at the time of vaccination (acute disease is defined as the presence of a moderate or severe illness with or without fever). All vaccines can be administered to persons with a minor illness such as diarrhoea, mild upper respiratory tract infection with or without low-grade febrile illness, i.e. axillary temperature of  $<37.5^{\circ}\text{C}$  ).
- b. Axillary temperature of  $\geq 37.5^{\circ}\text{C}$  at the time of vaccination.
- c. Any clinically significant abnormal finding on screening from biochemistry or haematology at 19 weeks.
- d. History of allergic disease or reactions likely to be exacerbated by any component of the vaccine, e.g. egg products.
- e. Presence of any underlying disease that compromises the diagnosis and evaluation of response to the vaccine.
- f. Invasive bacterial infections (pneumonia, meningitis).
- g. Any other on-going chronic illness requiring hospital specialist supervision.
- h. Administration of immunoglobulins and/or any blood products within one month preceding the planned administration of the vaccine candidate.
- i. Any history of anaphylaxis in reaction to vaccination.
- j. Research physician's assessment of lack of willingness by parents to participate and comply with all requirements of the protocol, or identification of any factor felt to significantly increase the infant's risk of suffering an adverse outcome.
- k. Likelihood of travel away from the study area.
- l. Untreated malaria infection.
- m. Any other clinical evidence of infection.

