### Visit 4 – FOLLOW-UP VISIT Week 1 (±2 days) post vaccination (Infant aged 21 weeks ± 10 days)

- Subjects will be brought to the vaccine trial clinic.
- Continued consent to participate in the study will be confirmed.
- An interim medical history will be taken.
- Physical examination including vital signs (temperature, respiratory rate, pulse rate), and anthropometry (weight, mid left upper arm circumference (MUAC), length) will be performed by the research field worker / research nurse.
- The injection site will be inspected by the research physician and local reactogenicity including the largest diameter of any induration or redness will be documented into the CRF.
- Adverse events that may have occurred since the infant was vaccinated and any concomitant medications will be documented in the CRF.

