#### **11.2.3 Immunogenicity of EPI vaccines**

The MVA.HIVA will be given at week 20 (4 weeks after the last EPI vaccines) so as to avoid the possibility of vaccine interference. However, vaccine antibody levels will be measured one week before and one week after MVA.HIVA (i.e. 5 weeks after the last EPI vaccines) to assess for gross interference of the MVA.HIVA vaccine with the immunogenicity of the EPI vaccines. Antibody responses to the EPI vaccines will be compared between Groups 1 and 2, with particular focus on the immunogenicity of Hib, which is the least immunogenic of the EPI vaccines and for which antibody levels below 0.5 micrograms per litre are considered unprotective.

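### Visit 3 is windowed by infant age alone, so MVA.HIVA can be given in window less than 28 days after the last EPI doses, against the protocol's own four-week minimum

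*Protocol*

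**What the plan says.** Section 4 states the minimum interval: the design looks at MVA.HIVA and "its gross impact on the immunogenicity of EPI vaccines administered not less than 4 weeks before". Section 11.2.3 gives the reason, placing the vaccine at week 20, "4 weeks after the last EPI vaccines) so as to avoid the possibility of vaccine interference".

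The operating rules are in sections 4.2 and 6.2:

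- Visit 1 is "SCREENING VISIT (Infant aged 16 weeks $\pm$ 10 days"). At this visit "EPI vaccines appropriate for age will be given (Pentavalent, PCV-7 and OPV"). These are the last EPI doses before MVA.HIVA.
- Visit 1 ends with an appointment for three weeks later, and Visit 2 with one for a week after that. Neither has a tolerance or a minimum.
- Visit 3 is "MVA.HIVA vaccination day (Infant aged 20 weeks $\pm$ 10 days"). It has no window counted from the EPI doses.
- Section 4.2 sets the recall by age. Infants attend at 19 weeks for the baseline bleed, and then "they will be asked to return to the Health Centre at 20 weeks of age".

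The inclusion criteria (5.1) ask that the EPI vaccines have been received under the national programme. Section 4.2 adds that they were given on schedule, without a tolerance. The exclusion criteria (5.2), which also serve as the contraindications to vaccination, contain no EPI interval. The Visit 3 checks cover consent, eligibility, blood results, history and examination.

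**The concern.** The four-week gap is a deliberate design feature. It recurs in the objectives and in the definition of the primary immunogenicity outcome (section 8), and section 11.2.3 gives it a protective purpose. Yet clinic staff who follow the printed age windows and the recall in 4.2 can vaccinate an infant earlier than four weeks after EPI without any rule in 5.1, 5.2 or 6.2 flagging it.

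The protocol writes such rules elsewhere. Exclusion h bars immunoglobulins or blood products "within one month preceding the planned administration of the vaccine candidate", and Visit 4 is defined as "FOLLOW-UP VISIT Week 1 (±2 days) post vaccination" as well as by age. The EPI-to-MVA.HIVA interval has no equivalent.

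Two things are at stake. A precaution stated for infants depends on someone remembering section 4 on the day. And an in-window visit under 28 days departs from the regimen under study, while the schedule gives no prompt to notice or record it.

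**Working it through.** **Inputs, in days of age**

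| Visit | Protocol 6.2 | Centre | Window |
|---|---|---|---|
| 1 (last EPI doses) | 16 weeks ± 10 days | 16 × 7 = 112 | 102–122 |
| 2 (baseline bleed) | 19 weeks ± 10 days | 19 × 7 = 133 | 123–143 |
| 3 (MVA.HIVA) | 20 weeks ± 10 days | 20 × 7 = 140 | 130–150 |
| 4 (week 1 bleed) | 21 weeks ± 10 days | 21 × 7 = 147 | 137–157 |

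The required minimum from section 4 is 4 × 7 = 28 days. Write V1, V2 and V3 for age in days at Visits 1, 2 and 3.

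**1. The plan's own figure.** The nominal gap is 140 − 112 = 28 days, which reproduces the stated four weeks.

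**2. What the windows permit.** Gap = V3 − V1.

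- Shortest: 130 − 122 = 8 days. It remains possible with an in-window bleed one week before vaccination (days 122, 123, 130).
- Longest: 150 − 102 = 48 days.
- There are 21 × 21 = 441 in-window day pairs. A pair falls below 28 days when the Visit 3 offset from its centre is smaller than the Visit 1 offset, which is 21 × 20 / 2 = 210 pairs. This counts calendar combinations and does not forecast attendance.

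**3. Recall by age, as in 4.2 (V3 = 140).** Gap = 140 − V1 = 28 − days late at Visit 1.

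| Visit 1 | V1 | Gap |
|---|---|---|
| On time | 112 | 28 days |
| 1 day late | 113 | 27 days |
| 5 days late | 117 | 23 days |
| 10 days late | 122 | 18 days |

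The sequence V1 = 117, V2 = 133, V3 = 140 is in window at every visit, matches the ages in 4.2 exactly, has the bleed 7 days before vaccination, and gives 23 days.

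**4. Recall by appointment, as in 6.2.** V3 = V1 + 21 + 7 = V1 + 28, which gives exactly 28 days with nothing to spare. One day early in total gives 27 days, and V1 + 27 lies in 130–150 for 20 of the 21 Visit 1 ages. One day early at each of the two appointments gives 20 + 6 = 26 days, still in window for an on-time or late Visit 1.

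**5. The two recall rules disagree whenever V1 is not 112.** For V1 = 117, section 6.2 points to 117 + 28 = day 145 and section 4.2 to day 140. Only day 145 meets the minimum, and the protocol does not say which rule governs.

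**6. Is a 28-day floor feasible?** The compliant Visit 3 days run from max(130, V1 + 28) to 150.

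| V1 | First compliant day | Compliant days out of 21 |
|---|---|---|
| 102 | 130 | 21 |
| 112 | 140 | 11 |
| 117 | 145 | 6 |
| 122 | 150 | 1 |

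For all 21 Visit 1 ages, V1 + 21, V1 + 28 and V1 + 35 fall inside the Visit 2, 3 and 4 windows.

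**The case against.** The best reply is that section 6.2 does schedule by interval: three weeks and then one week place vaccination 28 days after Visit 1 at any Visit 1 age, always in window. On that view 4.2 is a loose narrative using nominal ages. The 18- and 23-day cases need the appointments to be set aside, the 8-day case more so, and the realistic residual is 26 or 27 days. Section 4 also remains part of the protocol, so a shorter gap would be a deviation, and the study team gives the EPI doses itself and holds the date.

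Part of this stands. An infant who keeps both appointments to the day gets 28 days, and the 8-day figure is only a boundary. But the appointment lines set no floor, so attending one day early breaches section 4 while staying in window. They also conflict with 4.2 for any infant not seen on day 112, and 4.2 is the section that governs randomisation. Holding the EPI date is not the same as being told to check it.

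The limits on consequence also stand. Randomisation is at Visit 3, so short gaps should fall alike in both groups. The EPI comparison is secondary and looks only for gross interference. The borderline Hib signal in section 2.2.4 (p = 0.06 at the 0.5 cutoff, p = 0.39 at 1.0) came from co-administering a different MVA vaccine with the third EPI dose. Nothing in the protocol shows harm or interference at one to four weeks.

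**Conclusion.** The point holds. The protocol states a minimum of 28 days, but its visit windows and its age-based recall permit less. An infant seen late at Visit 1 and recalled at 20 weeks is in window at 18 to 27 days. A one-day-early return under the appointment scheme gives 27 days. The windows alone reach down to 8 days.

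This assumes that four weeks means 28 days and that the age windows are applied as printed. The protocol gives no distribution of visit dates, so the number of infants affected is unknown. The consequence is limited: departure from a stated precaution and regimen, and some added noise in the EPI antibody comparison, with no between-group bias expected. Gaps of 28 to 48 days comply and are not criticised. It should be fixed because the remedy is cheap and the precaution concerns infants, not because it threatens the trial's conclusions.

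**What to change.** - **Section 6.2, Visit 3:** define the visit as infant aged 20 weeks ± 10 days and at least 28 days after the recorded date of the Visit 1 EPI doses.
- **Visit 3 checks:** confirm that interval in both groups before the randomisation envelope is opened, so that the groups stay comparable.
- **Section 4.2:** recall the infant at 20 weeks of age or 28 days after the Visit 1 EPI doses, whichever is later, and keep the baseline bleed one week before.

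The cost is one line in each section and one checklist item. No age window needs widening, and no infants, visits or samples are added by design. A few infants may need re-booking. The tightest case is an infant seen on day 122, who has a single compliant day (day 150). A missed appointment there means a documented deviation or no randomisation.

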### **Preparation, Administration and Dosage of Study Intervention/Investigational Product**

The batch of the vaccine, MVA.HIVA, will be provided in vials of 200  $\mu\text{l}$  at a concentration of no less than  $5 \times 10^8$  pfu/ml in 10 mM Tris buffer, 0.9% NaCl. The dose of MVA.HIVA to be used in this stage will be  $5 \times 10^7$  pfu.

On the vaccination day, vaccines will be transported to Sukuta Health Centre in a cold box containing dry ice. It will be allowed to thaw to room temperature before use, and administered within 60 minutes of thawing. One vaccine vial per subject to be vaccinated will be used. The vaccine will be administered intramuscularly over the deltoid region of the left arm (the usual site of BCG vaccination). The physician will draw up the vaccine and the volume drawn will be checked and signed for onto the CRF by the physician and one other member of staff at Sukuta Health Centre (physician / nurse or field worker). The physician will wear gloves and eye protection when drawing up and administering the vaccine. Subjects will stay in the health centre for observation for at least 60 minutes after vaccination. During administration of the vaccines, medicines and resuscitation equipment will be immediately available for the management of anaphylaxis.

In order to minimise dissemination of the recombinant vectored vaccine virus into the environment the inoculation site will be covered with a dressing 10 minutes after immunization. This should absorb any virus that may leak out through the needle track. The dressing will be removed from the injection site at the end of the 60 minute observation period and will be disposed as GMO waste by autoclaving and incineration, in accordance with the relevant SOP and current standard practice at MRC, The Gambia.

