## **CONFIDENTIAL**

clinically significant. The following laboratory parameters will be monitored during the course of this study (as previously outlined): full blood count (FBC), creatinine and ALT.

Expected local reactions to the vaccine will not be recorded as an adverse event, but will be recorded on the CRFs. These include:

- Redness
- Induration
- Scaling / Blistering / Ulceration
- Axillary lymph node enlargement
- Pain (scored as follows)
  - 0 No pain
  - 1 Painful to touch
  - 2 Partial restriction of activities
  - 3 Unable to use the arm

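### MVA.HIVA goes into the BCG-scarred left arm, but no pre-injection recording of that site or axilla is specified, and no matching reading in controls

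*Protocol*

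**What the plan says.** - **Injection site.** Section 6.2, Visit 3, gives the vaccine "intramuscularly into the deltoid muscle of the left arm with a BCG scar". Section 7 (preparation and administration) places it "over the deltoid region of the left arm (the usual site of BCG vaccination").
- **BCG in all infants.** Section 4.2 limits recruitment to "Those with a documented BCG vaccination within the first two weeks of life who have received all their EPI vaccines on schedule".
- **Before injection.** Visits 1, 2 and 3 each list "Physical examination including vital signs (temperature, respiratory rate, pulse rate), and anthropometry (weight, mid left upper arm circumference (MUAC), length"). The BCG site and the axilla are not named.
- **After injection, Visit 3.** "The injection site will be inspected at 10 minutes when a dressing will be applied". Then, "The largest diameter of any induration or redness and any other local reaction at 1 hour will be documented into the CRF".
- **Follow-up.** At Visits 4, 5 and 6 the research physician inspects the injection site. Visits 4 and 5 record the largest diameter of any induration or redness, and Visit 6 records findings. None of these is defined as a change from an earlier reading.
- **What counts as a local reaction.** Section 9.1 lists redness, induration, scaling/blistering/ulceration, pain and "Axillary lymph node enlargement". They go on the CRF and are not recorded as adverse events.
- **How it is used.** Section 8 includes reactogenicity in the primary safety outcome. Section 11.2.1 compares it between MVA.HIVA recipients and controls. Controls receive no vaccine at Visit 3.

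**The concern.** The protocol itself says that the injection goes into the arm and region used for BCG. Several of the listed local findings, notably scaling, ulceration and an enlarged axillary node, are not specific to MVA.HIVA in such an arm. To interpret one of them at week 1, 8 or 16, the reader needs either the state of the same arm before injection or the same reading in infants who were not injected. The protocol specifies neither.

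The error can run in both directions. A finding that pre-dates the injection may be recorded as a vaccine reaction. A true flare of the BCG site after MVA.HIVA may be dismissed as old, although section 9.1 counts worsening of an existing condition as an adverse event. Section 2.3.1 also says that local reactions in earlier MVA.HIVA studies cleared on their own within days. An old finding noted at week 8 or 16 could then look like an unusually persistent reaction in infants.

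This cannot be left to the analysis plan. A reading that was never taken cannot be recovered in analysis.

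**Working it through.** **Step 1. Which comparison is available?** The readings the protocol specifies, set side by side:

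| Time | Vaccinees (n = 24) | Controls (n = 24) |
|---|---|---|
| Visits 1-3, before randomisation | General examination; site and axilla not named | Same |
| Visit 3, 10 minutes | Site inspected | No injection site |
| Visit 3, 1 hour | Induration/redness diameter and other local reaction on CRF | No injection site |
| Days 1-2 at home | Safety and reactogenicity, timed from MVA.HIVA vaccination | Not clearly covered |
| Visits 4-6 | Injection site inspected and documented | No injection site |

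A change from before injection cannot be computed from these readings. A between-group contrast needs a control value that the protocol does not clearly ask for.

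**Step 2. How large could the effect be?** The protocol states no figure, so there is none to reproduce. What follows is illustration only.

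Inputs: n = 24 vaccinees (section 4.1); b = prevalence of a residual BCG-site or left axillary finding at about 20 weeks, *assumed* at 1%, 5%, 10% and 20%; t = true vaccine reaction rate, *assumed* at 5%. Background and vaccine findings are taken as independent, and background findings as still present when read.

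- Expected number of vaccinees with a background finding: 24 × b.
- Chance of at least one: 1 − (1 − b)^24.
- Apparent reaction rate in vaccinees: 1 − (1 − t)(1 − b). For b = 10%: 1 − 0.95 × 0.90 = 14.5%.

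| b (assumed) | Expected of 24 | P(at least 1) | Apparent rate, t = 5% | Excess over 5%, in points |
|---|---|---|---|---|
| 1% | 0.24 | 0.21 | 5.95% | 0.95 |
| 5% | 1.2 | 0.71 | 9.75% | 4.75 |
| 10% | 2.4 | 0.92 | 14.5% | 9.5 |
| 20% | 4.8 | 0.995 | 24.0% | 19.0 |

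**Step 3. What would a control reading do?** If controls' left arms are not read, their recorded rate is 0 and the between-group difference carries the whole excess. If they are read in the same way, their expected rate is b, and the difference is [1 − (1 − t)(1 − b)] − b = t(1 − b). That gives 4.95%, 4.75%, 4.5% and 4.0% for the four values of b, close to the assumed 5%. A like-for-like control reading therefore removes most of the distortion on average.

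It does not do so for a single trial of this size. At b = 10% the number of infants with a background finding has variance 24 × 0.1 × 0.9 = 2.16 per group, so the difference between groups has standard deviation √(2 × 2.16) ≈ 2.1 infants. The baseline reading is still needed to interpret the individual infant.

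**The case against.** The case on the other side has real weight.

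- *The arm is seen before injection.* The examination at Visits 1 to 3 is introduced by a word that leaves the list open. Staff measure left arm circumference at each of these visits, and under section 7 a physician administers the vaccine. A reader might infer that nobody looks at the site until after injection; the protocol does not support that. What stands is that no **recording** is specified. An unrecorded look gives nothing to compare with, and injecting the deltoid does not involve examining the axilla.
- *The 1-hour reading is a partial baseline.* This is fair for ulceration, scaling or a node noted then, which could hardly be an hour old. It is weaker for redness and induration, which the injection and dressing may already have altered. Nodes are not named at that time point, and controls have no such reading.
- *Randomisation balances BCG findings.* It does so in expectation, but this helps only if controls are read in the same way, and the follow-up visits mention only the injection site.
- *Exclusions e and m in section 5.2* (disease that compromises evaluation of response; other clinical evidence of infection) may remove some infants with an active lesion. Neither names the BCG site or axilla.
- *The CRF or SOPs may hold such a field.* They are not shown, so this is possible. The photographs mentioned in section 14.2 have no stated time point. A primary safety comparison should not depend on a field that the protocol does not require.
- *Consequences are limited.* These findings are not AEs, analyses are mainly descriptive, and no test or sample-size figure depends on them. This stands, and it limits the severity.

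**Conclusion.** The point holds as a gap in what the protocol requires to be recorded. Followed as written, the plan gives a reactogenicity comparison, part of the primary safety outcome, with no recorded pre-injection state of a site already used for BCG and no specified reading of the same site in controls.

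Its size is unknown. The range of 0.24 to 4.8 of 24 vaccinees rests wholly on assumed prevalences of 1% to 20%. The protocol gives no rate of residual BCG lesions or nodes at this age and mentions only a scar. The direction follows for any background prevalence above zero if controls are not read.

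Two stronger readings are tempting and should be resisted. One is that local reaction rates will be inflated by some 20 percentage points; that merely restates the top of the assumed range. The other is that BCG findings will enter the adverse event counts or trigger the halting rule; section 9.1 keeps expected local reactions out of the AE record, and the rule in section 9.3 turns on a SUSAR. The change should be made, but the point does not call the trial's overall safety assessment into question.

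**What to change.** - At Visit 3, before the envelope is opened, record for every infant the left deltoid/BCG site (largest diameter of redness and of induration; scaling, blistering or ulceration) and left axillary nodes, on the CRF page used later.
- At Visits 4, 5 and 6, take the same readings of the left deltoid and axilla in **both** groups, and word the visit text by anatomical site so that it applies to controls.
- In section 11.2.1, define a local reaction for analysis as new or increased from the pre-randomisation reading, and compare its frequency between groups.

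Taking the first reading before allocation is known keeps it free of knowledge of the group. This matters because the study is open in the field.

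The cost is one CRF page and about a minute of examination per visit, by staff who already examine the infant and measure the left arm. The dose, injection site, visits and blood sampling are unchanged.
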